**Methods:**

The intervention consists of bilateral high-definition tRNS (HD-tRNS) over the auditory cortex combined with the application of AS which is studied in a crossover design. The visits will be performed in 26 sessions. There will be 20 treatment sessions, divided into two blocks: active and sham HD-tRNS. Within the blocks, the interventions are divided into group A: HD-tRNS and AS, and group B: HD-tRNS alone. Furthermore, in addition to the assessments directly following the intervention sessions, there will be six extra sessions performed subsequently at the end of each block, after a period of some days (follow-ups 1 and 2) and a month after the last intervention (C). Primary outcome measures are analog scales for evaluation of subjective tinnitus loudness and distress, and the audiological measurement of minimum masking level (MML). Secondary outcome measures are brain activity as measured by electroencephalography and standardized questionnaires for evaluating tinnitus distress and severity.

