**Discussion:**

To the best of our knowledge, this is the first study which uses HD-tRNS combined with AS for tinnitus treatment. The crossover design permits the comparison between HD-tRNS active vs. sham and with vs. without AS. Thus, it will be possible to evaluate the efficacy of the combined approach to HD-tRNS alone. In addition, the use of different objective and subjective evaluations for tinnitus enable more reliable and valid results.

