The second block of the study consists of Treatment Period 2 and Follow-up 2. This block has the same characteristics in the procedure and performance time as the previous sessions (from 2 to 13), the difference is the type of stimulation of HD-tRNS, which contrasts with the one previously carried out (Active/Sham). In session 14, the second period of treatment starts, and the same assessments are made as in session 2. Sessions 15–22 are treatment sessions. In session 23, the same assessments are made as in session 11. Follow-up 2 occurs in sessions 24 and 25, with the same characteristics as follow-up 1 (Fig. 4).

The Close-out is performed in session 26, 7 days after Follow-up 2 and approximately 1 month after Treatment 2 (Fig. 4). In this last session, the primary, secondary, and other outcome measures are performed.

The intervention and evaluation procedures, as well as the explanations regarding the choice of paradigms, can be found in detail below:

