#### Acoustic stimulation (AS)

For acoustic stimulation, WN with an intensity of MML + 10 dB is used. The AS is also applied for 20 min and will never surpass 85 dB SPL at the ears.

For Sham AS, deep pure tones at SL + 10 dB are used, varying randomly between [1] 100 and 200 Hz [2], 1.33 and 4 Hz presentation rate [3], randomly varying in intensity ± 10% around the SL + 10 dB level, and [4] randomly varying linear decay envelope between 250 and 750 ms. The AS sham condition is purposely constructed not to cover the tinnitus pitch range and to present very low sound energy, so as not to be able to generate tinnitus suppression. The randomization of frequency, temporal, and intensity parameters ensures the absence of any regularities (including musical properties).

The AS is performed using Etymotic ER-2 research-grade, air conduction in-ear headphones (Etymotic Research Ins., USA), as with these it is possible to get quasi-linear response in frequencies up to 14 kHz compared to other air tube headphones. The intention behind the use of these headphones for AS and the auditory paradigm is to optimize the transmission of the acoustic signals and the absence of ferromagnetic metal in respect to not interfere the EEG measurements or tES being provided at the same time.

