## Assignment of interventions: Blinding

### Who will be blinded {17a}

Participants and researchers performing the treatments and measurements will be blinded. The information about the course of the training is kept identical for participants in both groups: the position of the electrodes is the same, and the duration of stimulations and sessions are the same for both groups. In addition, the current in the sham condition is applied during the first and last 30 s of stimulation as a ramp up and ramp down, respectively, thus the participant feels a tingling sensation similar to the active stimulation. TRNS and AS is programmed in such a way that the study personnel are blinded to the active or sham status of these interventions.

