### Methods for additional analyses (e.g., subgroup analyses) {20b}

Each intervention group will also be compared separately using LME and respective post hoc tests when necessary. This will be to observe the effect of HD-tRNS alone and bimodal stimulation (HD-tRNS and AS associated).

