In addition, a central novelty of the study is the use of a HD-tRNS allowing greater precision of the target location through the use of 17 HD electrodes. The wide range of audiometric and tinnitometric measurements will allow us to build subgroups based on hearing exams as well as other outcome measures and enable more reliable and valid results. Reactivity to residual inhibition for example could give insights on treatment effects of the acoustic stimulation and help to determine best clinical practices. Another theoretical advance may be considered in the assessment of individual tinnitus frequency through pitch matching which then forms the basis of the ERP paradigm. With a neural response on individually adjusted pure tones, further neuroplastic changes in the auditory cortex after the HD-tRNS can be explored. The paradigm is an iteration of a recent study by [53]. In more detail, we expect a normalization of ERP responses in tinnitus sufferers [90]. Ideally, collected data will therefore contribute to the discussion of pathological auditory perception and finally may act as a biomarkers or classifiers of chronic tinnitus patients [51].

With the double-blinded crossover design, it will be possible to evaluate the efficacy of HD-tRNS and bimodal stimulation compared to sham conditions. The between-subject comparison will allow us to investigate the added value of combined stimulation and the unspecific effect of any acoustic input during tES. The use of double-blind design enables a proper evaluation of the treatment approaches by reducing biasing influences of the study personnel. Unfortunately, the design does not include a branch with acoustic stimulation only and a control group of healthy hearing matched participants is also missing. These shortcomings are due to the focus of the study as well as resource and infrastructure limitations. It was thus decided to focus on the effectiveness of electric stimulation and its combination with acoustic stimulation. Supplementary long-term follow-up measurements could additionally contribute further efficacy data of bimodal stimulation in reducing tinnitus loudness and distress.

Among the limitations, it might be necessary to consider the individual anatomical brain characteristics of each participant and different brain areas as potential targets [4–7] instead of using a generalized approach based on the localization of Rademacher et al. [43].

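### The protocol describes arm A's comparator in two ways; if AS switches to sham together with HD-tRNS, the HD-tRNS effect is identified only in arm B and the claimed comparisons need narrowing

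*Protocol article*

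**What the plan says.** Several places in the protocol article bear on what changes between arm A's two blocks.

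- Abstract, Methods: "There will be 20 treatment sessions, divided into two blocks: active and sham HD-tRNS", and "Within the blocks, the interventions are divided into group A: HD-tRNS and AS, and group B: HD-tRNS alone". The blocks are defined by the current; AS appears as a fixed feature of group A.
- Intervention description {11a}: the second block repeats the first, and "the difference is the type of stimulation of HD-tRNS, which contrasts with the one previously carried out (Active/Sham"). AS is not mentioned.
- Study intervention(s) group A: the active condition is HD-tRNS with AS; the sham condition is sham HD-tRNS with sham AS. Both components switch.
- Study intervention(s) group B: active or sham HD-tRNS, with no sound in either condition.
- Acoustic stimulation (AS): "For Sham AS, deep pure tones at SL + 10 dB are used". Sham AS is thus audible.
- Who will be blinded {17a}: "TRNS and AS is programmed in such a way that the study personnel are blinded to the active or sham status of these interventions".

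Three places say what the trial will deliver.

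- Abstract, Discussion: "The crossover design permits the comparison between HD-tRNS active vs. sham and with vs. without AS".
- Main Discussion: the between-subject comparison is to "investigate the added value of combined stimulation and the unspecific effect of any acoustic input during tES". The same section concedes that there is no AS-only branch.
- Methods for additional analyses {20b}: each arm is also analysed separately, and "This will be to observe the effect of HD-tRNS alone and bimodal stimulation (HD-tRNS and AS associated").

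**The concern.** The two descriptions imply different estimands for the arm that carries the primary objective. If only the current changes, arm A's active-minus-sham contrast is the effect of HD-tRNS in the presence of real sound. If both components change, it is the effect of the whole package against a double sham.

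The difference matters on the protocol's own terms. AS is white noise at MML + 10 dB, the stimulus and level that the Residual inhibition section uses to reduce tinnitus. The background section says such inhibition can be induced in most sufferers, and sham AS is designed to be unable to suppress tinnitus. A difference between AS and sham AS is therefore to be expected, although its duration is unknown. Under the double-sham listing, that difference enters any HD-tRNS conclusion that uses arm A.

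**Working it through.** **Notation.** The reference is sham current without sound. T = effect of active HD-tRNS without sound; W = effect of real AS under sham current; S = effect of sham AS under sham current; I = any extra effect when real AS is combined with active HD-tRNS. Arm differences are taken as zero in expectation by randomisation, and period and carry-over effects are set aside.

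**Cell means if the group A listing stands**

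| Cell | Current | Sound | Mean |
|---|---|---|---|
| A, active block | active | real AS | T + W + I |
| A, sham block | sham | sham AS | S |
| B, active block | active | none | T |
| B, sham block | sham | none | 0 |

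**What these cells identify**

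- B active − B sham = T: HD-tRNS alone, within subject.
- A active − A sham = T + W + I − S: the package against double sham.
- A active − B active = W + I: AS added to active HD-tRNS.
- A sham − B sham = S: sham AS against no sound, under sham current.
- Difference between arms in active minus sham = W + I − S. It contains no T.

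**What they do not identify**

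- T + I, the HD-tRNS effect in the presence of real AS.
- W and I separately.
- The effect of sham AS under active current, because no cell pairs the two. A check of the rank of the four-cell design confirms each of these.

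**Pooling over arms.** With equal arms, [(T + W + I − S) + T]/2 = T + (W + I − S)/2. If the AS contribution W + I − S were 0.25, 0.5 or 0.75 SD (assumed values), the pooled contrast would be off for T by 0.125, 0.25 or 0.375 SD.

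**If only the current changes.** The sham-block mean in arm A becomes W. Then A active − A sham = T + I, A sham − B sham = W, and the between-arm difference is I. T, W and I are all identified; S is not. The two descriptions therefore lead to different sets of permissible conclusions.

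**Sample behind the HD-tRNS effect.** Sample size {14} gives 40 recruited, 20 per group, and dropout of up to 25%. Arm B has 20, and 20 × (1 − 0.25) = 15.

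The plan's own figure of 32 reproduces for the two-group interaction if the correlation between repeated measures is 0.5, which the protocol does not state. The noncentrality is f²·N·m/(1 − ρ) = 0.0625 × 32 × 5/0.5 = 20, with 4 and 120 degrees of freedom, and power is 0.957. The required N would be 62, 44 or 20 for ρ = 0, 0.3 or 0.7. That calculation does not size arm B's own contrast.

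As an illustration, consider a paired two-sided 5% t test with ρ = 0.5 assumed:

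| Standardised difference | n = 15 | n = 20 | n = 40 |
|---|---|---|---|
| 0.5 | 0.44 | 0.57 | 0.87 |
| 0.8 | 0.82 | 0.92 | >0.99 |

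**The case against.** The best defence is that the conflict is one of omission. Neither the abstract nor {11a} says that nothing but the current changes. The group A listing, the specification of sham AS and the blinding section all point to AS switching too, and sham AS would otherwise have no use in the trial. Figs. 1 and 4, not available here, may show AS status by block. This makes one reading more likely, but the text still describes the comparator inconsistently, and a reader of the abstract or {11a} would take arm A's control to include real sound.

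A reader might also draw four stronger conclusions that the document does not support.

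- That the HD-tRNS effect cannot be estimated. It can, within arm B, and {20b} plans analyses by arm.
- That the trial will report a pooled active-versus-sham contrast as the HD-tRNS effect. No section specifies one; the bias shown arises only if it is run.
- That the added-value claim fails. A active versus B active gives W + I, which is added value over HD-tRNS alone. The article does not claim to isolate statistical synergy, and it discloses that an AS-only branch is missing.
- That the unspecific effect of sound is unobservable. It is observable under sham current.

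One might also be tempted to play sham AS in arm B to fill the missing cell. That would remove the HD-tRNS-alone condition on which the stated comparisons depend, so it is not recommended.

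Finally, residual inhibition is called temporary, and the adherence section has questionnaires completed before sessions, although the abstract also mentions assessments directly after them. How far AS carries through to the outcomes is therefore unknown; only the algebra is certain.

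**Conclusion.** The concern holds as an inconsistency in arm A's comparator with defined consequences for what may be concluded. If AS switches with HD-tRNS:

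- HD-tRNS versus sham rests on arm B alone, about half the sample.
- Arm A's contrast is a package effect.
- A contrast pooled over arms would be confounded with AS by (W + I − S)/2.
- AS added to active HD-tRNS is estimable, but synergy cannot be separated from AS alone.
- The unspecific acoustic effect is available only under sham current, so the Discussion's reference to sound during tES reaches further than the design does for active stimulation.

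The identification results need only the listed cells and randomisation between arms. The SD and power figures rest on assumed values.

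**What to change.** Make the abstract and {11a} agree with the group A listing, or the listing with them, so that arm A's comparator is stated once. If the listing stands:

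1. Take the HD-tRNS-versus-sham conclusion from arm B and name that contrast among the main ones; at present the by-arm analyses appear only as additional analyses.
2. State that an active-versus-sham contrast pooled over arms will not be used as the HD-tRNS effect.
3. Label arm A's active-versus-sham contrast as the effect of the package.
4. Describe the between-arm difference in the active condition as AS plus any interaction.
5. Restrict the comparison claims in the abstract and Discussion accordingly, with the unspecific acoustic effect limited to sham HD-tRNS.

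Items 1 to 5 change wording and contrast definitions only; they need no new participants or procedures and can be settled before analysis. The cost is a narrower HD-tRNS claim with the lower precision of about 15 to 20 participants.

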#### High-definition transcranial random noise stimulation (HD-tRNS)

The medical device (MD) used for HD-tRNS in this study is a Soterix Medical Multichannel Neuromodulation Stimulator (MxN-33 system, model-no. 3200C; Soterix Medical Inc, New York, USA).

Stimulation is directed to the primary auditory cortex bilaterally [42], over Heschl’s gyrus. Localization is supported by Rademacher et al. [43] in the standard MNI coordinate system.

The Talairach coordinates of the location are reflected in the center of Heschl’s gyrus, with the targeted MNI voxels *x* = − 42, *y* = − 21, *z* = + 7 for the left and *x* = + 46, *y* = − 13, *z* = + 8 for the right side (Figs. 2 and 3). Targeting was optimized with respect to the mentioned target voxel and upper limit of total current (i.e., 2 mA) with Soterix Software MxN HD resulting in a target current of 0.095 V/m in the left and 0.072 V/m in the right target of interest.

**Fig. 2 Fig2:**
[figure not shown]
Sites of stimulation in HD-tRNS. Adapted from the manual of the system 10/20 [44, 45]. Created from the HD-Targets Software of Soterix Medical Multichannel Neuromodulation Stimulator (MxN-33 system; model-no. 3200C)

**Fig. 3 Fig3:**
[figure not shown]
Positioning of the electrodes in HD-tRNS. Based on the 10/20 system for EEG

lf-tRNS frequency range (0.1–100 Hz) will be used with seventeen channels corresponding to the positioning of the electrodes in the 10/20 system [44, 45] and their respective amplitudes TP7 (0.69 mA), T8 (0.78 mA), T7 (0.53 mA), PZ (0.05 mA), PO10 (0.17 mA), P4 (0.15 mA), IZ (0.06 mA), FC3 (0.22 mA), FC1 (0.16 mA), EX18 (0.18 mA), EX17 (0.25 mA), EX4 (0.05 mA), CP2 (0.07 mA), CP1 (0.20 mA), C2 (0.10 mA), C1 (0.21 mA), and O10 (0.12 mA) (Figs. 2 and 3). The stimulation will be applied for 20 min (totaling 21 min with ramp up and ramp down).

#### Acoustic stimulation (AS)

For acoustic stimulation, WN with an intensity of MML + 10 dB is used. The AS is also applied for 20 min and will never surpass 85 dB SPL at the ears.

For Sham AS, deep pure tones at SL + 10 dB are used, varying randomly between [1] 100 and 200 Hz [2], 1.33 and 4 Hz presentation rate [3], randomly varying in intensity ± 10% around the SL + 10 dB level, and [4] randomly varying linear decay envelope between 250 and 750 ms. The AS sham condition is purposely constructed not to cover the tinnitus pitch range and to present very low sound energy, so as not to be able to generate tinnitus suppression. The randomization of frequency, temporal, and intensity parameters ensures the absence of any regularities (including musical properties).

The AS is performed using Etymotic ER-2 research-grade, air conduction in-ear headphones (Etymotic Research Ins., USA), as with these it is possible to get quasi-linear response in frequencies up to 14 kHz compared to other air tube headphones. The intention behind the use of these headphones for AS and the auditory paradigm is to optimize the transmission of the acoustic signals and the absence of ferromagnetic metal in respect to not interfere the EEG measurements or tES being provided at the same time.

#### Electroencephalogram (EEG)—resting state

EEG is recorded with a Biosemi ActiveTwo EEG system (MarkII System, Biosemi, Amsterdam, the Netherlands) with 128 electrodes in a sound-proof and electrically shielded room. Impedances are kept below 20 kOhm. Electrodes are located according to the international 10/20 system [44, 45].

The participant is positioned in a relaxed posture and position, in front of a computer screen showing a fixation cross at eye level. The participant is told to relax and do nothing. There now follow 10 recordings of 60 s each, for a total of 10 min, with participant instructed to open and close their eyes by a soft female voice (https://tinnet.tinnitusresearch.net/images/pdf/WG3/Standardisation_Report_V5.pdf). A fixation cross is presented in open eye phases to fixate the gaze and counteract eye movements.

#### Electroencephalogram (EEG)—event-related potentials (ERP)

The Auditory Multifeature Paradigm, generated by transcriptions created in MATLAB Software (Mathworks, Natick, MA, USA) [46], is used.

Stimulus creation and presentation are performed with the Psychophysics Toolbox (PTB [47–49];) and a class-based library derivative o-PTB [50]. The research-grade, Etymotic ER-2 air conduction headphones are driven by Babyface Pro FS sound card (RME Fireface UCX; Audio AG, Haimhausen, Germany).

For each subject, two stimuli with different acoustics frequencies are presented, one at the tinnitus frequency, assessed by measurement of tinnitus pitch matching (see below), and one at 500 Hz as the standard frequency [51].

In contrast to the study of Mahmoudian et al. [52], we used pure tones (PT) instead of harmonic tones (HT) (3 partials) to ensure that the stimuli are fully heard at high frequencies, which would not be possible with HT with octaved partials (e.g. 8000, 16000, 24000).

Standard stimuli are composed of 1 sinusoidal 500 Hz tone with a total duration of 75 ms including 5 ms rise and 5 ms fall time (cosine ramp), as in the study by Asadpour et al. [53]. The same stimulus parameter set is used for the pitch-matched tinnitus frequency.

The parameters follow the auditory multi-feature paradigm by Näätänen et al. [54] who used 8 different types of deviant stimuli clustered in 5 different classes. Additionally, we added a sixth deviant class, namely PT in pink noise (PN), as seen in Pakarinen et al. [55]. The deviant tones differed from the standards in (1) Frequency—half of the frequency deviants were 10% higher, half 10% lower than the standard, (2) Intensity—half of the intensity deviants were + 10 dB and half − 10 dB compared to the standard, (3) Location—half of the deviants were mapped to the right channel and half to the left channel, (4) Duration—the duration deviant was 25 ms in length, (5) Silent gap in the middle of the tone—the gap deviant cuts out 7 ms from the middle of the standard stimulus, leaving a gap, and (6) Noise-level deviant—14 dB of PN added to the standard tone [55].

All stimuli are presented diotic at 40 dB above individual sensation Level (SL) for the two frequencies. The multi-feature paradigm consists out of 4410 tones in total and can be divided in 6 sequences (3 per frequency) which are presented in a pseudo-randomized fashion, starting with either 500 Hz or the tinnitus frequency sequence. Each sequence starts with 15 standards, followed by 60 blocks of 12 tones. The blocks include each deviant class once and every second tone is a standard. Between the blocks, the same deviant class never follows each other. In total, 735 tones are presented per sequence, so 2205 tones per frequency leading to a set of 1080 data points of deviants. Every class of deviants has the same probability of occurrence. The stimuli are presented with a stimulus onset asynchrony (SOA) of 500 ms. This means that every 500 ms from onset a tone was presented regardless of its length, keeping a 120 bpm rhythm. Every sequence lasts 367.5 s. With 10 s of break between each block, the full duration of the entire paradigm is 2245 s (~ 37 min).

## Audiometry

Audiometry comprises pure tone audiometry (PTA), loudness discomfort level (LDL), isometric forward masking contour (IFMC), temporal masking curve (TMC), and sensation level (SL) of the ERP stimuli. The tests were performed using MATLAB Software (Mathworks, Natick, MA) [46], a modified multiThreshold toolbox (University of Essex, UK), Babyface Pro FS sound card (RME Fireface UCX; Audio AG, Haimhausen, Germany), and headphones model AKG K271 MK II (AKG Acoustics, Northridge, USA). The SL is performed using Etymotic ER-2 research-grade, air conduction in-ear headphones (Etymotic Research Ins., USA) with 13 mm ear tips.

